## Proposed study to compare two nutritionally equivalent fortifiers

The Puffin study is designed to compare two nutritionally equivalent dietary approaches, by comparing the use of standard cow milk fortifiers (CMBF, control) to that of using human milk fortifier (HMBF, intervention).

- **Setting**: Three tertiary level NICUs
- **Population**: preterm infants <32 weeks or <1500g tolerating milk feeds
- **Control**: use of CMBF from full feeds (tolerating 150mls/kg/day for 1-2 days)
- **Intervention**: use of HMBF from full feeds
- **Primary outcome**: stool inflammatory markers (calprotectin) after 3 weeks exposure
- **Study design**: non-blinded randomised controlled trial
- **Timeframe**: until 36 weeks corrected gestation or when fortifier no longer required whichever is earlier

### Inclusion and Exclusion criteria

To be included, infants must have been born at <32 weeks gestation and/or <1500g and be tolerating full milk feeds for at least 24 hours. Infants who have any congenital abnormalities that affect feeding, or who have had gut surgery or a diagnosis of necrotising enterocolitis (NEC), will be excluded. In addition, infants who have been exposed to formula milk or breastmilk fortifiers before randomisation will be excluded.

Randomisation

Infants will be randomised using minimisation incorporating the following variables: hospital site, gestation (<28 weeks), and multiple birth status; this will be held and coordinated by the Newcastle research team using an internet based secured randomisation system. Contact and allocation will be by password protected internet access. Infants will be allocated to either standard fortification (control) or human based fortification (intervention). Multiples (twins and higher order) will be randomised to the same trial arm.

### Primary and key secondary outcomes

We will determine stool inflammatory profile by measuring fecal calprotectin after 1 and 3 weeks of exposure (primary outcome) and a panel of fecal cytokines using a multiplex assay (<https://www.mesoscale.com/products/v-plex-human-biomarker-54-plex-kit-k15248d/>) similar to that used in recent studies exploring the impact of probiotics in VPT infants.[10] We will also determine fecal microbiota proportions using 16s RNA next generation sequencing as used in our previous studies[11] and secretory IgA (sIgA) levels in stool.

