# Study summary

This is a protocol for an Investigator Initiated trial, commercially part-funded, non-blinded, randomised controlled trial comparing two nutritionally equivalent methods of breastmilk fortification in healthy preterm infants. The dietary regimes involve fully supporting mothers to provide their own expressed breast milk and using donor human milk to make up shortfall in breastmilk supply. The primary outcome is the level of inflammatory markers in the stool. Parents of infants on neonatal units (Newcastle upon Tyne, Middlesbrough and Southampton) will be approached by clinical team members, and infants will be enrolled after signed informed consent. The study starts when infants are stable and tolerating full milk feeds and finishes prior to hospital discharge and will last for around 3-6 weeks per baby on average.

| Title (Acronym) | **PUFFIN – Preterm Milk Fortification in Neonates** |
| --- | --- |
| Study centres | Ward 35, Royal Victoria Infirmary, Newcastle upon Tyne (lead site)  James Cook University Hospital, Middlesbrough  University Hospital Southampton |
| Study objectives | To compare two comparable methods of fortifying mother’s own breastmilk and/or donor human milk |
| Study design | Randomised, minimised, open label, controlled trial |
| Study population | Inclusion criteria   - Stable preterm infants born <32 completed weeks of gestation or <1500g birthweight tolerating full milk feeds for at least 24 hours - Written informed consent from parents - Maternal intention to continue providing breastmilk - Agreement to use breast milk fortifier   Exclusion criteria   - Parents unwilling to consent - Exposure to formula milk or breastmilk fortifiers before randomisation - Known congenital anomaly affecting the GI tract (gut) - Previous gut surgery or diagnosis of necrotising enterocolitis (NEC) |
| Interventions | Standard commercially available breastmilk fortifier derived from bovine source added to breast milk (control) compared to commercially available fortifier derived from human milk (intervention) |
| Duration | From full milk feeds until fortifier no longer required, or 36 weeks corrected gestation (whichever is earlier) |
| Target number of patients | 36 infants with complete sampling (18 infants per trial arm): recruitment of up to 50 infants may be needed to achieve this |

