| Randomisation | Minimisation using gestation (<28 weeks yes/no) and hospital site. Twins and triplets will be allocated to same study arm. Secured, password protected web-based randomisation using minimisation algorithm ([www.sealedenvelope.com](http://www.sealedenvelope.com) or similar) |
| Primary outcomes | Stool inflammatory marker (calprotectin) |
| Secondary outcomes | Fecal cytokine levels  16s gut microbiota profile  sIgA in stool  Urinary inflammatory markers (iFABP and similar)  Feed tolerance and growth-related outcomes  Neonatal morbidities and clinical outcomes |
| Duration of trial intervention | 36 weeks postmenstrual age or when fortifier no longer required (whichever earlier) |
| Duration of study | Recruitment period: 12 months  Total trial duration: 15 months |
| End of Trial | Discharge from neonatal unit |
| Safety assessments | Routine assessments until discharge from Neonatal Unit  Safety tracking during hospitalisation |

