### Sample size and Power

We hypothesise that use of a HMF will result in lower levels of fecal calprotectin, and a panel of fecal cytokines and that this will also be associated with greater abundance of Bifidobacteria using 16s gut microbiota analysis. Calprotectin levels in preterm infants vary depending on the presence of neonatal disease but are typically between 4 and 6±2mg/dL[12]. To determine a 50% reduction in fecal calprotectin levels we will study the primary outcome assessment in 36 infants using 5% significance and power of 80%. Allowing for dropouts and other reasons we aim to recruit between 40-50 infants across three NICU sites.

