## Trial registration, Ethics, HRA and risk burden

The trial will be an Investigator Initiated trial registered on ISRCTN prior to opening sponsored by Newcastle Hospitals NHS Foundation Trust. We will apply for HRA and REC approvals and apply for adoption onto the NIHR portfolio. The trial is an open-label study of two comparable diets and is not a CTIMP. There are no specific ethical issues with this trial, but we recognise the additional burden placed on parents by being asked to consider trial enrolment. There are no specific safety or risk issues as part of the trial *per se* as all milk and products (donor milk, donor milk fortifier, cow milk-based fortifier, mother’s own milk) are already given routinely to babies. No additional interventions or tests are required for infants to join the trial, but we will seek permission to collect an extra sample of blood at the same time as venepuncture is required for any clinical reasons on two occasions. Parents can choose to decline the additional targeted blood samples but still participate in the trial as all other tests are non-invasive. The trial is fully compliant with national recommendations and Baby Friendly Initiative (BFI) part of UNICEF.

Patient withdrawal

Temporary discontinuation of the intervention is at the discretion of the attending clinician.

Permanent discontinuation is possible at parental request at any point, or after transfer to a non-participating site, and may be accompanied by permission to continue to collect data or not. Data already obtained will be included in all analyses.

Trial product

Standard cows milk based fortifiers in current use in each recruiting unit will be utilised by each site in the control arm, and be subject to standard vitamin and mineral supplementation in use in that unit, or as suggested in Appendix 4 if no current guidance exists. Infants randomised to human based fortifier will use NeoKare Maternal Milk Fortifer (MMF) and the vitamin and mineral supplementation outlined in Appendix 4. In all trial arms supplementation should then be adjusted with routinely measured blood results. Infants in both trial arms where insufficient maternal milk is available should receive donor human milk until at least D21 of the study (primary study end point). Thereafter if there is shortfall in maternal milk supply supplementation with donor milk or formula is at the discretion of the attending clinicians.

Adverse events

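### The protocol contradicts itself on the primary time point for faecal calprotectin: weeks 1 and 3, week 3 alone, or study day 21

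*Protocol*

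**What the plan says.** The Protocol describes the primary outcome in several places, and they do not agree on its timing.

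- *Study summary*, opening paragraph: "The primary outcome is the level of inflammatory markers in the stool". It names neither marker nor time.
- *Study summary*, table, primary outcome row: "Stool inflammatory marker (calprotectin". No time is given. The secondary outcomes row lists "Fecal cytokine levels".
- *Proposed study to compare two nutritionally equivalent fortifiers*: "stool inflammatory markers (calprotectin) after 3 weeks exposure". Week 3 only.
- *Primary and key secondary outcomes*: "We will determine stool inflammatory profile by measuring fecal calprotectin after 1 and 3 weeks of exposure (primary outcome". Weeks 1 and 3.
- *Trial registration, Ethics, HRA and risk burden*, under Trial product: infants short of maternal milk "should receive donor human milk until at least D21 of the study (primary study end point". Study day 21.
- *Additional secondary outcomes*, sampling table: calprotectin at enrolment and days 7, 14 and 21, with none marked as primary.
- *Sample size and Power*: "we will study the primary outcome assessment in 36 infants using 5% significance and power of 80" per cent. No time is given.

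**The concern.** The section that exists to define the outcomes attaches the primary label to two time points, while two other sections attach it to one. No statement says how weeks 1 and 3 would be combined: success on either, success on both, an average, or a repeated-measures comparison. Those choices differ in error rate and power, and the sample size section does not say which was assumed.

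There is a second, smaller discrepancy in the clock. Two sections count weeks of exposure and one counts days of the study. The two agree for an infant fortified without a break from enrolment. They can part in two situations that the Protocol itself allows: a temporary stop at the clinician's discretion (Patient withdrawal), and an end of intervention before 21 days, because fortifier is no longer needed or 36 weeks is reached (Study summary).

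What is at stake is the meaning of the 5% significance level. In an open-label trial, the time point and clock that carry the primary test should be settled before any result is seen.

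**Working it through.** **Inputs.** From Sample size and Power: control level 4 to 6 with ±2 mg/dL, a 50% reduction, 5% significance, 80% power. From the Study summary: 18 infants per arm. Assumptions: ±2 is an SD, the test is two-sided, and the correlation between week 1 and week 3 (not given) is varied.

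**1. Reproducing the 36.** At mean 4 the difference is 0.5 × 4 = 2.

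n per arm = 2 × (1.960 + 0.842)² × (SD/difference)² = 2 × 7.85 × (2/2)² = 15.7, so 16 per arm, 32 in total.

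- t-test: 17 per arm, 34 in total.
- t-test with a Mann-Whitney allowance: 17/0.955 = 17.8, so 18 per arm, 36 in total.
- t-test at mean 5 (difference 2.5): 24 in total; at mean 6 (difference 3): 18 in total.
- One-sided t-test at mean 4: 28 in total.

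The stated 36 therefore fits one two-sided 5% comparison at the low end of the range. Power of that test at 18 per arm, mean 4, is 83% (t-test).

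**2. Two time points, either counts, each at an unadjusted 5%.** If independent, family-wise error = 1 − 0.95² = 9.75%. With correlated normal test statistics:

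| Assumed correlation | Family-wise error |
| --- | --- |
| 0 | 9.75% |
| 0.3 | 9.5% |
| 0.5 | 9.1% |
| 0.7 | 8.35% |
| 0.9 | 7.05% |

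**3. Two time points, either counts, alpha split at 2.5% each.** The standardised shift at 18 per arm is difference/(SD × √(2/18)) = 3.00, 3.75 and 4.50 at means 4, 5 and 6. The critical value rises from 1.960 to 2.241.

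| Control mean | Power per test, normal | Power per test, t-test |
| --- | --- | --- |
| 4 | 78% | 74% |
| 5 | 93% | 91% |
| 6 | 99% | 98% |

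Restoring 80% per test at mean 4 takes 21 per arm, 42 in total, by t-test (20 per arm, 40 in total, by the normal formula).

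**4. Both time points required, each at 5%.** There is no alpha inflation. Assuming the same effect at both weeks, joint power (normal) at mean 4 is 72% to 78% for correlation 0 to 0.7; at mean 5 it is 93% to 94%.

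**5. The clock.** If exposure means days actually fortified, an infant paused for five days (an illustrative figure) reaches 21 days of exposure at about study day 26. The donor-milk provision under Trial product is guaranteed only to day 21, after which formula may be used, so the two definitions can sample an infant under different feeding. Entry is open to infants under 1500 g whatever their gestation. One who starts after 36 − 3 = 33 weeks cannot complete three weeks of exposure before the 36-week limit, but can still have a day-21 sample if in hospital.

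**The case against.** The strongest reply is that the intended outcome is fairly clear. Two sections agree on week 3 or day 21, the sampling table works by fixed days, and the week 1 mention may be loose drafting. Analysis method and multiplicity rule commonly belong in the statistical analysis plan, which is not shown. This has force on seriousness, since the repair is a few words. It does not remove the point: the conflict is between statements in the Protocol, and an analysis plan could settle it only by overriding one of them.

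Four stronger readings are tempting, and the documents do not support them.

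- A reader might infer that the false-positive rate exceeds 5%. Nothing says that success on either time point would count. A both-required rule or a single repeated-measures test would not inflate alpha.
- A reader might infer that the plan is underpowered. The 74% arises only if alpha is split and only at mean 4; at means 5 and 6 the same split leaves more than 90%.
- A reader might infer that several markers are primary, from the plural in the Study summary. The design list uses the same plural with calprotectin in brackets, calprotectin is the only marker named as primary, and cytokines are listed as secondary. This is wording to tidy.
- A reader might infer that pauses move or cancel the primary sample. No section says so. What stands is a difference in wording that can matter for individual infants.

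**Conclusion.** The point holds as an internal contradiction. The Protocol states its primary time point in incompatible ways, and its clock in two. The planned 36 is not shown to be wrong; it is consistent with one primary test, and the Protocol does not fix which test that is. The cost of leaving this open depends on the rule later adopted: family-wise error of about 7% to 9.75% if either time counts unadjusted; power per test of 74%, 91% or 98% at means 4, 5 and 6 if alpha is split; no error inflation if both are required, with joint power of 72% to 78% at mean 4. These figures rest on ±2 being an SD, a two-sided test and assumed correlations; the joint power also assumes equal effects at the two weeks.

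**What to change.** Put one statement in the Study summary (paragraph and table), the design list, Primary and key secondary outcomes, Sample size and Power, and Trial product: *Primary outcome: faecal calprotectin at study day 21; one two-sided 5% test.* This matches the Trial product text and the day-based sampling table. Define day 0 of that clock, for example as randomisation or first fortified feed. Make day 7 and day 14 calprotectin secondary, and replace the plural marker wording in the Study summary with calprotectin.

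If two primary time points are really intended, keep both, state the error-control rule (either with adjusted alpha, both required, or one combined test) and restate the power for that rule.

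The single-time-point option changes wording only and leaves the 36 as it is. Its small downside is that week 1 can no longer carry a primary claim. With two time points, the number may need to rise, for example to 40 to 42 at mean 4 with alpha split equally.

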### Additional secondary outcomes – growth and neonatal outcomes

We will collect a range of relevant secondary outcomes:

1. Growth – weekly weight, length and head circumference, absolute changes (g/kg/day and mm/week) and change in standard deviation score based on UK reference data from study enrolment until 36wca and/or discharge
2. Episodes of NEC, sepsis - confirmed and clinically suspected according to existing nationally agreed case definitions
3. Chronic lung disease, Retinopathy of prematurity (ROP), Intraventricular haemorrhage, Cystic PVL etc.
4. Days of intensive, high and low dependency care; age at discharge, total length of stay
5. Age at starting fortifier; tolerance, days not received due to intolerance, duration of breastfeeding; type of feeding at discharge (direct breast feeding, tube feeding etc.) etc.
6. Blood/urine work, serum biochemistry and other inflammatory and immune markers (blood and urine): hsCRP, lymphocyte subsets, plasma amino acids (PAA), where samples and funding allow

|  | Enrolment (baseline) | Day 7 | Day 14 | Day 21 | 36w or discharge | Total per infant |
| --- | --- | --- | --- | --- | --- | --- |
| Growth | x | x | x | x | x | 5 |
| Calprotectin | x | x | x | x |  | 4 |
| Stool cytokines |  | x |  | x |  | 2 |
| Stool 16s RNA | x | x |  | x |  | 3 |
| Stool sIgA | x | x |  | x |  | 3 |
| Urine inflammatory/ oxidative measures | x | x | x | x | x | 5 |
| Feeding tolerance etc. | x | x | x | x | x | 5 |
| Targeted bloodwork (PAA etc) |  | x |  | x |  | 2 |
| Clinical outcomes / safety | x | x | x | x | x | 5 |

### Sample size and Power

We hypothesise that use of a HMF will result in lower levels of fecal calprotectin, and a panel of fecal cytokines and that this will also be associated with greater abundance of Bifidobacteria using 16s gut microbiota analysis. Calprotectin levels in preterm infants vary depending on the presence of neonatal disease but are typically between 4 and 6±2mg/dL[12]. To determine a 50% reduction in fecal calprotectin levels we will study the primary outcome assessment in 36 infants using 5% significance and power of 80%. Allowing for dropouts and other reasons we aim to recruit between 40-50 infants across three NICU sites.

## Funding

We have acquired funding support from NeoKare to cover the costs of study delivery, fecal assays and 16s RNA analysis (total costs provided £50,000) and supply of HMF product free of charge. The remaining non-consumable costs will be limited because there is no other change to clinical practice, and we will collect electronic clinical data extracted from e-record and Badger neonatal database which will be inputted into an excel worksheet. Trial recruitment will be conducted by a GCP member of neonatal research staff supported by the neonatal research nurse. Costs additional to £50,000 (e.g urinary assays etc) will be met out of existing departmental research funds.

## Commercial involvement

NeoKare will play no role in any aspect of trial conduct, and all data will remain the property of NHS Hospitals who will undertake data collection and analysis along with established collaborators at Newcastle University. Newcastle lead site will develop a contract with NeoKare to allow them sight of any data prior to publication but the right to publish study findings will rest entirely with the research team. NeoKare will retain full IP of their product.

## Trial registration, Ethics, HRA and risk burden

The trial will be an Investigator Initiated trial registered on ISRCTN prior to opening sponsored by Newcastle Hospitals NHS Foundation Trust. We will apply for HRA and REC approvals and apply for adoption onto the NIHR portfolio. The trial is an open-label study of two comparable diets and is not a CTIMP. There are no specific ethical issues with this trial, but we recognise the additional burden placed on parents by being asked to consider trial enrolment. There are no specific safety or risk issues as part of the trial *per se* as all milk and products (donor milk, donor milk fortifier, cow milk-based fortifier, mother’s own milk) are already given routinely to babies. No additional interventions or tests are required for infants to join the trial, but we will seek permission to collect an extra sample of blood at the same time as venepuncture is required for any clinical reasons on two occasions. Parents can choose to decline the additional targeted blood samples but still participate in the trial as all other tests are non-invasive. The trial is fully compliant with national recommendations and Baby Friendly Initiative (BFI) part of UNICEF.

Patient withdrawal

Temporary discontinuation of the intervention is at the discretion of the attending clinician.

Permanent discontinuation is possible at parental request at any point, or after transfer to a non-participating site, and may be accompanied by permission to continue to collect data or not. Data already obtained will be included in all analyses.

Trial product

Standard cows milk based fortifiers in current use in each recruiting unit will be utilised by each site in the control arm, and be subject to standard vitamin and mineral supplementation in use in that unit, or as suggested in Appendix 4 if no current guidance exists. Infants randomised to human based fortifier will use NeoKare Maternal Milk Fortifer (MMF) and the vitamin and mineral supplementation outlined in Appendix 4. In all trial arms supplementation should then be adjusted with routinely measured blood results. Infants in both trial arms where insufficient maternal milk is available should receive donor human milk until at least D21 of the study (primary study end point). Thereafter if there is shortfall in maternal milk supply supplementation with donor milk or formula is at the discretion of the attending clinicians.

Adverse events

As this is not a clinical trial of a medicinal product and the intervention, and its delivery, are considered safe and already available to purchase we do not anticipate any adverse reactions due to the trial intervention (use of donor breast milk based fortifier). However, this is a very high risk patient group and some infants may develop serious complications e.g. sepsis or necrotising enterocolitis and some may die. We will record all serious adverse events (SAE). Serious adverse events that may occur include:

• Outcomes recorded and reported as part of the study: necrotising enterocolitis (NEC), sepsis, intraventricular haemorrhage, periventricular leukomalacia, retinopathy of prematurity, chronic lung disease, feeding intolerance (number of days when nil by mouth i.e. no enteral intake or fortification pasued), and death.

• Outcomes that commonly occur in this population but that will not be specifically recorded or reported as part of this study include: abnormal electrolytes, bone chemistry, liver functions tests or other routine biochemistry or haematology; transfusion of blood or related products; complications related to use of intravenous catheters (e.g. misplacement or malfunction); presence of and/or treatment for a patent ductus arteriosus; requirement for surgery and/or provision of an intestinal or airway stoma, intraventricular shunt; vomiting, gastro-oesophageal reflux, constipation, diarrhoea, skin or nappy rash.

Data queries, missing data

Where infants are transferred to other hospitals before the end of the study (36 weeks corrected age) the investigators will make contact with that hospital and request to collect data. The data collected will already form part of the infants’ medical record and can be extracted from clinical records or clinical databases e.g. the National Neonatal Research Database that holds data from the Badger system. The data will include feeding information (e.g. type of milk and supplements), growth (e.g. weight, length and head circumference), any important medical outcomes (e.g. infection episodes, requirement for respiratory support) and duration of hospital stay.

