# Appendix 1: data items and definitions

At randomisation

• Date and time of birth

• Sex

• Confirmation of eligibility (full eligibility check)

• Date of parental consent

• Name of person taking consent

• Gestational age (in weeks and days)

• Recruiting hospital

• Study allocation

Baseline evaluation

• Birth weight (kg)

• Birth length (cm)

• Head circumference (cm)

• Ethnicity (NHS Ethnicity)

• Mode of delivery

• Use of antenatal steroids

• Date and time first trial intervention administered

Daily evaluations

• Record nutritional intake (type of feed, fortification and type)

- If fortification paused, reason

• If infant is nil by mouth and reason

• Check for SAE

• Record of withdrawal information if relevant

Weekly evaluations

• Weight (kg)

• Length (cm)

• Head circumference (cm)

End of study evaluation

• Weight (kg)

• Length (cm)

• Head circumference (cm)

We will use standard definitions of disease and outcomes refined and validated in our previous studies to collect data including

- Standardized forms for: NEC/gut complications; sepsis

Appendix 4

Suggested mineral and vitamin supplementation for CMBF and HMBF arms

Please note: adjustment should be made based on serum monitoring as routinely undertaken for preterm infants

| Arm | CMBF | HMBF | Age/point at commencement |
| --- | --- | --- | --- |
| Supplement |  |  |  |
| Dalivit | 0.3ml | 0.6ml | From full feeds |
| Vitamin K drops | Not needed | 50mcg | From full feeds |
| Iron | As per unit guidance | As per unit guidance | From 2 weeks after last transfusion or 4 weeks whichever later |
| Folate |  | 40mcg (0.5 ml) | From full feeds |

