Appendix 5 Nutritional content of fortifiers

| **Nutrients** | **Unit** | **Mature human milk** 100 mL** | **NeoKare MMF/g** | Mature human milk 100 mL + 4 g (4 sachets) NeoKare MMF |
| --- | --- | --- | --- | --- |
| Energy | KJ Kcal | 289 69 | 17.99 4.30 | 360.96 86.20 |
| **Macronutrients** |  |  |  |  |
| Fat | g | 4.1 | 0.18 | 4.82 |
| Saturated fatty acids | g | ns | 0.08 | 0.33 |
| Carbohydrate | g | 7.2 | 0.4 | 8.80 |
| of which sugar (Lactose) | g | 7.2 | 0.34 | 8.56 |
| Protein | g | 1.3 | 0.27 | 2.38 |
| Salt (=sodiumx2.5) | g | 0.04 | 0.004 | 0.06 |
| **Vitamins** |  |  |  |  |
| Vitamin A | µg | 58 | 1.96 | 65.84 |
| Vitamin D | µg | trace | 0.018 | 0.072 |
| Vitamin E | mg | 0.34 | 0.0204 | 0.422 |
| Vitamin K | µg | ns | 0.024 | 0.096 |
| Vitamin C | mg | 4 | <0.001 | 4 |
| Thiamine (Vitamin B1) | mg | 0.02 | <0.001 | 0.02 |
| Riboflavin (Vitamin B2) | mg | 0.03 | 0.002 | 0.038 |
| Niacin (Vitamin B3) | mg | 0.2 | 0.044 | 0.376 |
| Vitamin B6 | mg | 0.01 | <0.0005 | 0.01 |
| Folic acid | µg | 5 | <0.1 | 5 |
| Vitamin B12 | µg | trace | 0.004 | 0.014 |
| Biotin (Vitamin B7) | µg | 0.7 | <100 | 0.7 |
| Pantothenic acid (Vit B5) | mg | 0.25 | NA | 0.25 |
| **Minerals** |  |  |  |  |
| Sodium | mg | 15 | 1.685 | 21.74 |
| Potassium | mg | 58 | 7.81 | 89.24 |
| Chloride | mg | 42 | 4.91 | 61.65 |
| Calcium | mg | 34 | 19 | 110.0 |
| Phosphorus | mg | 15 | 11 | 59.00 |
| Magnesium | mg | 3 | 1.57261 | 9.29 |
| Iron | mg | 0.07 | 0.003 | 0.08 |
| Zinc | mg | 0.3 | 0.036 | 0.44 |
| Copper | mg | 0.04 | 0.0035 | 0.054 |
| Manganese | mg | trace | 0.00022 | 0.001 |
| Fluoride | mg | ns | NA | ns |
| Selenium | µg | 1 | 0.203 | 1.812 |
| Chromium | µg | ns | <0.5 | <2 |
| Molybdenum | µg | ns | <0.10 | <0.4 |
| Iodine | µg | 7 | 0.73 | 9.94 |

**
[figure not shown]
**

| **Please complete for infants with at least 5 days NBM, gut surgery or abdominal diagnosis resulting in death** | | | | | | |
| --- | --- | --- | --- | --- | --- | --- |
| **PUFFIN ID:** | | | | | | |
| Onset of the episode: day when abdominal concerns were raised and enteral feeds stopped (dd/mm/yy) | | | | | -- / -- / -- | |
| End of the episode: day when enteral feeds restarted (dd/mm/yy) or infant died if before feeds restarted | | | | | -- / -- / -- | |
| **What was the diagnosis? (please tick ONE box only)** | | | | | | |

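### The adverse-event section promises to record every SAE, then puts surgery, stoma and shunt on a not-recorded list, although gut surgery triggers the trial's own Gut Form

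*Protocol*

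**What the plan says.** The Adverse events text (Protocol, under Trial registration, Ethics, HRA and risk burden) opens with an undertaking that carries no exception: "We will record all serious adverse events (SAE"). The next sentence begins "Serious adverse events that may occur include" and introduces two bullets.

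- The first bullet is collected: "Outcomes recorded and reported as part of the study: necrotising enterocolitis (NEC), sepsis, intraventricular haemorrhage", followed by periventricular leukomalacia, retinopathy of prematurity, chronic lung disease, feeding intolerance and death.
- The second bullet is not: "Outcomes that commonly occur in this population but that will not be specifically recorded or reported as part of this study include". Its items run from routine laboratory abnormalities to nappy rash, and among them is "requirement for surgery and/or provision of an intestinal or airway stoma, intraventricular shunt".

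Two other places bear on this. Appendix 1 has a daily SAE check and plans "Standardized forms for: NEC/gut complications; sepsis". The Gut Form, among the reporting forms at the end of the protocol, carries the instruction "Please complete for infants with at least 5 days NBM, gut surgery or abdominal diagnosis resulting in death".

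**The concern.** An operation, a stoma and a shunt are introduced as SAEs, covered by a promise to record all SAEs, and then placed among events that are not specifically recorded or reported. A site reading this section alone could reasonably make no SAE entry for a gut operation. A site reading the Gut Form would complete it for the same operation. A site relying on the opening promise would log an SAE as well.

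The by-arm safety table would then depend partly on which sentence each of the three units followed. The trial studies gut inflammation, and the protocol's own case for it, under Patient Public Involvement, rests in part on NEC that needs surgery. Surgery is therefore an awkward item to leave ambiguous.

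**Working it through.** No arithmetic applies: the protocol gives no event rate for surgery, stoma or shunt, and the point does not depend on alpha, power or sample size. The check is a comparison of the texts.

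**Step 1: is the adverse-event section consistent with itself?** The promise covers all SAEs. Both bullets hang from the one sentence that introduces SAEs. The second bullet withholds specific recording and reporting. Read literally, its items are SAEs, will all be recorded, and will not be specifically recorded. These statements agree only if the second bullet exempts events from separate outcome reporting and not from SAE recording. The text does not say so. Nor do the visible adverse-event section and Appendix 1 give seriousness criteria by which a site could decide. The bullet does not sort by seriousness either, since surgery stands beside constipation and skin rash.

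**Step 2: is it consistent with the forms?** Event by event:

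| Event | Adverse-event lists | Visible Gut Form | Result |
|---|---|---|---|
| NEC | Recorded | Staged diagnosis boxes | Captured |
| Feeding intolerance | Recorded | Form triggered at 5 or more days nil by mouth | Captured |
| Death | Recorded | Form triggered if from an abdominal diagnosis | Captured |
| Focal intestinal perforation | Not named | Diagnosis box | Captured if the form is triggered |
| Gut surgery | Not-recorded list | Triggers the form by itself | Contradiction |
| Intestinal stoma | Not-recorded list | Implies gut surgery, so the form is triggered, but there is no stoma field | Operation captured, stoma itself not |
| Airway stoma | Not-recorded list | Outside the form's scope | No visible form |
| Intraventricular shunt | Not-recorded list | Outside the form's scope | No visible form |
| Other non-gut surgery | Not-recorded list | Outside the form's scope | No visible form |

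**Step 3: does the daily SAE check close the gap?** Only in part. It prompts staff to look for SAEs every day, but the definition they bring to it is the section that contradicts itself. For the last three rows it is the only route visible in the protocol.

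**The case against.** The strongest reply is that the second list is simply a list of common, expected events exempted from separate reporting, placed under a careless lead-in. The word specifically supports this, and so do items such as reflux and nappy rash, which nobody would ordinarily call serious. On that reading a serious event is still caught by the opening promise and the daily check. This may well be what was intended, and it reduces the defect from an instruction to omit to an ambiguity. It does not remove the ambiguity, because no sentence says that a listed event which is serious must still be recorded.

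A reader might infer more: that serious gut events will be lost from a trial of gut inflammation. The documents do not support that. NEC, feeding intolerance and death are on the recorded list. Gut surgery alone triggers the Gut Form, which also covers focal perforation, septic ileus and other diagnoses and has a date field for a diagnosis made at surgery. Figures next to the forms are not shown, so further fields cannot be excluded.

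A reader might also see a clash between the exclusion of abnormal routine biochemistry and the secondary outcome "Blood/urine work, serum biochemistry and other inflammatory and immune markers (blood and urine"). That fails as well. The outcome is collected only where samples and funding allow, and measuring an analyte as an outcome is compatible with not reporting each abnormal routine result as an event.

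**Conclusion.** The contradiction stands, within the adverse-event section and between that section and the Gut Form. Its practical reach is narrow: inconsistent classification of gut surgery as an SAE across the three sites, and incomplete capture of stoma formation, airway stoma, shunt and other non-gut surgery. The primary outcome is unaffected. The correction should be made because the safety rule as written cannot be applied in one way.

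No percentage should be attached to this. The weight of a single event in a small arm, or the upper bound after zero events, follows from the number of infants and is the same whatever the recording rule. Nor does the lack of a data monitoring committee strengthen the point, since a committee sees only what has been recorded.

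The conclusion assumes that the visible form text is substantially complete. That sites would in fact diverge is a risk inferred from the wording, not something the documents show.

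**What to change.** Reconcile the passages in three short edits:

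1. Remove surgery, intestinal or airway stoma and intraventricular shunt from the not-recorded list.
2. Add one sentence: any event remaining on that list that meets the SAE definition is still recorded as an SAE and tabulated by arm, and the list exempts events only from separate outcome reporting. Point to the SAE definition in use.
3. Align the adverse-event wording with the Gut Form, so that a gut operation leads to both the form and an SAE entry. An SAE entry would also capture the stoma without redesigning the form.

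The information is already in the clinical record, and the protocol already plans to extract clinical data electronically. The downside is a few more SAE entries. No additional sampling and no change to treatment or to the primary analysis is needed.
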